### Qualitative Evaluation

We shall aim to interview 15 patients from cohort 1 to obtain their views on the PRINT program, specifically on the implementation of the 5SPM method. We shall recruit participants who complete the 1-year follow-up but also some who might withdraw from treatment before then. In principle, the interviews will explore the following thematic questions: (1) To what extent the goals of personalized precision psychiatry based on pharmacogenetics were aligned with the patients’ own goals? (2) Did the PRINT program help in achieving their goals, what did not, and why? (3) Is there anything that could have been performed differently during the informed consent and 5SPM processes? (4) What might have contributed to nonengagement and treatment discontinuation? (5) What would help them meet their goals and priorities better and why?

As stated in the Patient and Public Involvement section, the CLUMP patient and carer advisory group will also contribute to the identification of additional themes for the qualitative evaluation.

Sampling will be purposive, with quota stratification by gender and clinical background, to enhance transferability through thick description of participant characteristics and context. The CLUMP project team will also be interviewed to characterize their perspectives on implementing the new model and triangulate experiences of model implementation. An independent researcher trained in qualitative methods will conduct all the interviews, which will be audio recorded and transcribed verbatim. Data analysis will be based on the constant comparative method [25]. This will involve intensive engagement with the data using comparison across datasets to generate higher-order themes with explanatory value. An audit trail—including coding logs, analytical memos, and interview minutes—will be maintained to support dependability and confirmability of findings. To strengthen credibility, this study will use data triangulation (patients and professionals), peer debriefing within the research team, and member checking with the patient and carer advisory group [26,27]. The NVivo software (QSR International) will be used to assist in coding the data.

### Economic Evaluation

We shall explore cost-benefit using the primary outcome measure: all-cause discontinuation. The time horizon will be 1 year after antipsychotic initiation for both cohorts. Costs and outcomes will be compared at the final follow-up point and presented as mean values with SDs by cohort. The costs will be estimated using service use data. We shall collect these data using an adapted Spanish-language version of the Early Intervention Adult Service Use Schedule [28], which contains costs that are easy to track and calculate in the Spanish health system. The Early Intervention Adult Service Use Schedule will be completed for both cohorts. This measure covers the use of all health and social care services over 12 months (with an interim collection at 6 months), as well as sociodemographic information and employment status. In cohort 1, we shall also conduct a cost-utility analysis using quality-adjusted life years derived from the EQ-5D-5L.

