### Clinical Management and Pharmacogenetics Analysis

Patients in cohort 1 will receive the recently introduced PRINT program, an early intervention in psychosis model, including the 5SPM method based on pharmacogenetics developed by our unit of pharmacogenetics and precision medicine at the HUS. As mentioned previously, the 5SPM method includes five steps: (1) collection of clinical, epidemiological, and treatment data; (2) study of pharmacological interactions based on drug-specific pharmacokinetic pathways; (3) pharmacogenetic analysis of the genes that code enzymes involved in drug-specific metabolism; (4) introduction of or change in pharmacotherapy according to the data obtained in the previous 3 steps; and (5) analysis of the treatment outputs and reassessment if needed. These steps will be preceded by an informed consent process. This preliminary procedure plus steps 1 to 4 will be conducted as soon as possible, ideally when a patient with a first episode of psychosis is identified by clinical services, aiming to minimize the time between the initial presentation and pharmacogenetics-informed decisions on pharmacotherapy. Step 5 (treatment review) will be carried out 6 months after antipsychotic treatment initiation. All steps will require a multidisciplinary approach and a shared decision-making process including patients or their family or legal representatives, especially if the patient lacks the mental capacity to make such decisions.

For the pharmacogenetics analysis (step 3), we shall use mass spectrometry and real-time polymerase chain reaction to study the genes encoding enzymes 1A2, 2B6, 2C9, 2C19, 2D6, 3A4, and 3A5 of the CYP450 family, in addition to transporter ABCB1. The CYP450 superfamily contains highly polymorphic genes. The usual approach to the relationship between genotypic variability and the metabolism of CYP450 substrates is based on the definition of metabolic phenotypes with their characteristic pharmacokinetic implications according to different genetic mechanisms. Metabolic profiles will be considered to make decisions on antipsychotic treatment choices. We already have enough technical support and pharmacogenetics evidence for most antipsychotics used in the early stages of a psychotic illness (ie, olanzapine, risperidone, paliperidone, quetiapine, aripiprazole, amisulpride, lurasidone, cariprazine, haloperidol, and zuclopenthixol).

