### Outcome Measures

#### Primary Outcome Measure

The primary outcome to measure treatment adherence will be all-cause discontinuation of the initially prescribed antipsychotic medication following the patient’s or treating clinician’s decision. All-cause discontinuation rates in the CLUMP project will be defined by all-cause discontinuation proportions during the 1-year follow-up and the mean time to such discontinuation.

For cohort 1, the 1-year follow-up period will start when an antipsychotic medication is prescribed taking into consideration the pharmacogenetics advice emerging from the 5SPM method. For cohort 2, follow-up would begin on the date when the first antipsychotic medication was prescribed. For both cohorts, the first prescribed antipsychotic will be the initially prescribed antipsychotic drug for maintenance treatment, not only for short-term use to control psychomotor agitation. In addition, in accordance with existing scientific consensus, the discontinuation date will be defined as the first day of a 2-week or longer interruption of the first prescribed antipsychotic. In cohort 2, treatment discontinuation dates will be determined by examining clinical records. Where only approximate dates are available, the first, middle, or final day of the month will be used as best estimates. In cases in which cross-titration of medication took place, the date of discontinuation will be the first day of the cross-tapering process.

All-cause discontinuation will also be stratified by 4 reasons: insufficient efficacy, adverse events, lack of adherence, and other. Insufficient efficacy will be established at the treating clinician’s judgment only after at least 3 weeks of treatment. If more than one reason for discontinuation was present, we shall select one by applying the ranking order as stated previously.

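### The 1-year cost window opens after the pharmacogenetic work-up and costs come only from service use data, so as written the cost of 5SPM steps 1 to 3 is largely not captured in cohort 1

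*Protocol article*

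**What the plan says.** Four statements in the protocol article bear on this point.

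- **Cost window** (Economic Evaluation): "The time horizon will be 1 year after antipsychotic initiation for both cohorts".
- **Cost source** (Economic Evaluation): "The costs will be estimated using service use data". The data come from an adapted Spanish-language service use schedule completed for both cohorts. On its coverage the article says: "This measure covers the use of all health and social care services over 12 months (with an interim collection at 6 months").
- **Start of the year** (Primary Outcome Measure). In cohort 1, "the 1-year follow-up period will start when an antipsychotic medication is prescribed taking into consideration the pharmacogenetics advice" that comes out of 5SPM. For the comparator: "For cohort 2, follow-up would begin on the date when the first antipsychotic medication was prescribed".
- **Order of the 5SPM steps** (Clinical Management and Pharmacogenetics Analysis). Consent comes first, then data collection (step 1), interaction study (step 2) and genotyping (step 3). Step 4 is "introduction of or change in pharmacotherapy according to the data obtained in the previous 3 steps". Then: "Step 5 (treatment review) will be carried out 6 months after antipsychotic treatment initiation".

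The fourth of the numbered objectives asks whether the new model brings cost benefits to the public health system and the wider economy. The fifth aims at a blueprint for use elsewhere.

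**The concern.** The work-up is the resource that distinguishes 5SPM from ordinary prescribing. An economic comparison that opens its books on the day of the resulting prescription, and records only service use from then on, counts what follows from the work-up but not the work-up itself. Cohort 2 was treated by generic community teams before PRINT existed, and the article describes no such work-up in that care. The omission therefore does not cancel between cohorts. It lowers the cohort 1 mean cost only, and so makes PRINT look cheaper than it is.

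At stake is the answer to objective 4, and any cost claim carried into the blueprint of objective 5.

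**Working it through.** The plan states no cost figure for this evaluation, so there is none to reproduce. The check is first one of timing, then simple algebra.

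**Timing, cohort 1**

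| Element | When, by the stated rules | In the 1-year window? |
|---|---|---|
| Consent process | before step 1 | No |
| Step 1, data collection | before the informed prescription | No |
| Step 2, interaction study | before the informed prescription | No |
| Step 3, genotyping | before the informed prescription | No |
| Step 4, informed prescription | day 0 | Opens it |
| Step 5, treatment review | month 6 | Yes |

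The table takes antipsychotic initiation, the term in the Economic Evaluation section, to be the date on which the cohort 1 follow-up year starts. The Statistical Analysis section supports this, because it counts the year of follow-up from treatment initiation. The two terms could separate for a patient who was already taking an antipsychotic when the advice arrived, since step 4 allows a change of treatment as well as a first prescription. If initiation then meant the earlier drug, the work-up could fall inside the window. The article does not say how many such patients are expected.

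**Algebra**

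Inputs:
- c = cost of the uncaptured work-up per cohort 1 patient. It is not given in the documents.
- Planning difference = 0.40 − 0.10 = 0.30 (Effect and Sample Size). The running text of that section gives 40% as the expected discontinuation and 10% as the target for PRINT. The numbered list attaches the two rates to the opposite cohorts, but the absolute difference is 0.30 either way.
- Expected size of cohort 1 = 50 (same section).

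Let D be the true difference in mean cost, cohort 1 minus cohort 2. If c is left out for every cohort 1 patient, the reported difference is D − c. Hence:
- incremental cost is understated by c per cohort 1 patient;
- the cohort 1 total is understated by 50 × c;
- cost per discontinuation avoided is understated by c/0.30 = 3.33c. At half the planning difference it is c/0.15 = 6.67c.

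For illustration only, with c assumed to lie between 100 and 1,000 euros:

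| Assumed c | Cohort 1 total (50c) | Per discontinuation avoided, difference 0.30 | Per discontinuation avoided, difference 0.15 |
|---|---|---|---|
| 100 | 5,000 | 333 | 667 |
| 300 | 15,000 | 1,000 | 2,000 |
| 500 | 25,000 | 1,667 | 3,333 |
| 1,000 | 50,000 | 3,333 | 6,667 |

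If the work-up is captured for a fraction f of cohort 1, the mean shift is (1 − f)c and every entry scales by 1 − f. The sign of the answer changes only if the reported saving per patient is smaller than the omitted mean cost.

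**The case against.** The strongest reply is that nothing in the article says the test is left out. The Economic Evaluation section is one paragraph of a condensed article and lists no cost items, so the absence of a line for genotyping does not prove exclusion. The schedule is adapted and is said to cover all health and social care services. A work-up done by a hospital unit inside a clinical programme could reasonably be recorded as a service. A time horizon is also not in itself a rule against costing the intervention, which is ordinarily charged at time zero.

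Much of this stands. A reader might infer that the plan counts the savings of 5SPM and none of its price. The documents do not support that: the month 6 review is inside the window, the work-up may be for patients already on a drug, and the content of the adapted schedule is not visible. A reader might also infer that the omission is large enough to decide objective 4. That is not supported either, because the article gives neither c nor total costs, and it describes the cost-benefit analysis as exploratory.

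The reply does not remove the combined effect of the two rules the article does fix. The schedule covers 12 months within a stated 1-year horizon, and the work-up precedes that horizon on the main pathway. No sentence brings it back in. This goes beyond a detail left to a fuller document: an analyst who followed the window and cost source as stated would leave the work-up out.

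**Conclusion.** The point holds in this form. Under the stated window and cost source, the cost of consent and of 5SPM steps 1 to 3 is not captured for most cohort 1 patients. Incremental cost is then understated by c for each patient affected, or about 3.3c per discontinuation avoided if the planning difference of 0.30 is realised and the omission applies throughout cohort 1. The error runs one way, in favour of PRINT.

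The conclusion rests on three assumptions: that antipsychotic initiation in the Economic Evaluation section means the informed prescription for most of cohort 1; that the adapted schedule does not reach back before that date; and that no intervention cost is added elsewhere. Its practical importance relative to admissions, visits and other service costs cannot be judged from the documents.

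It might also be inferred that the window should open at first presentation to services. The point does not require this. It would give patients windows of unequal length and separate the cost year from the primary outcome year, and charging the work-up directly corrects the omission without either drawback.

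**What to change.** Keep the 1-year window aligned with the primary outcome and add to the Economic Evaluation section a statement to this effect:

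- The full per-patient cost of 5SPM (consent, sampling, genotyping, interpretation and staff time) is charged to every cohort 1 patient at time zero, whenever it was incurred, and reported as a separate intervention cost line.
- Anything the service use schedule already records, such as the month 6 review or a work-up that falls inside the window, is counted once only.
- The 5SPM unit cost is varied over a stated range in a sensitivity analysis.

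The cost is a small micro-costing from the pharmacogenetics unit's own laboratory and staff records. The article expects data collection to run until June 2027, so there is time to do it. The downside for the investigators is that PRINT will look somewhat more costly. No change is needed to the follow-up dates, the sample size or the primary outcome.

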### Participants

A total of 300 patients will be included in this project. We shall include 2 different cohorts. Cohort 1 will be a prospective sample of patients with first-episode psychosis referred over 18 months to the new early intervention in psychosis program of personalized precision psychiatry (PRINT) at CAUSA. Cohort 2 will be a retrospective, consecutive (in reverse chronological order as registered in the CAUSA electronic health records) sample of patients who experienced a first episode of psychosis before the implementation of PRINT.

Inclusion and exclusion criteria for both cohorts will be aligned with the PRINT program referral acceptance criteria, which are predominantly inclusive.

Inclusion criteria are as follows: patients (1) with a diagnosis of first-episode psychosis, either nonaffective or affective; (2) aged 12 to 35 years; and (3) followed by clinical services for at least 1 year or earlier if there was evidence of antipsychotic treatment discontinuation (see the Outcome Measures section). In addition, patients in cohort 1 or their family or legal representatives will have to provide written consent to take part in the CLUMP project, including pharmacogenetics analysis (see the Ethical Considerations section). For patients in retrospective cohort 2, this will not be an inclusion criterion, but all of them will be approached by our research team seeking their consent to obtain their pharmacogenetic profile for research purposes.

Exclusion criteria are as follows: patients (1) with first-episode psychosis due to organic causes, for example, brain diseases such as Huntington or Parkinson disease, HIV, syphilis, dementia, brain tumors or cysts, or brain injury; (2) with moderate to severe intellectual disability; and (3) who spent (cohort 2) or plan to reside during (cohort 1) most of the 1-year follow-up period in a locality out of the PRINT program’s catchment area.

For additional comparative purposes, we shall analyze the environmental, clinical, and pharmacogenetic information of patients with psychotic disorders of more than 5 years of evolution or with other mental disorders whose data are currently stored and have been ethically approved for research use in our unit of pharmacogenetics and precision medicine at the HUS.

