#### Secondary Outcome Measures

We shall also collect pragmatic efficacy, tolerability, and functional outcome measures in both cohorts. These will include evaluations during the follow-up period regarding hospital admissions; visits to accident and emergency departments and outpatient clinics; changes in and number of medications; changes in antipsychotic dose over time; use of chlorpromazine dose equivalents as reference; type and number of side effects, including impact on BMI; and initiation or return to work or academic activities.

As part of routine practice, patients in cohort 1 will also be assessed using the quality-of-life self-completion questionnaire EQ-5D-5L to determine overall improvement over time. Scores from this questionnaire will also feed into the 5SPM step 5 to make treatment decisions at month 6. This cohort will also be evaluated using a battery of questionnaires, including the Positive and Negative Syndrome Scale [21], Calgary Depression Scale for Schizophrenia [22], Brief Negative Symptom Scale [23], and Udvalg for Kliniske Undersøgelser Side Effect Rating Scale [24].

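### The cost-utility analysis is confined to cohort 1, the only cohort with EQ-5D-5L data, so it has no comparator and cannot give an incremental cost per QALY

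*Protocol article*

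**What the plan says.** The protocol article plans two economic analyses in its Economic Evaluation section.

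- **Between cohorts.** "We shall explore cost-benefit using the primary outcome measure: all-cause discontinuation". On costs: "The costs will be estimated using service use data", and "The Early Intervention Adult Service Use Schedule will be completed for both cohorts". On the period: "The time horizon will be 1 year after antipsychotic initiation for both cohorts". Costs and outcomes are to be compared at the end of follow-up and shown as means with SDs for each cohort.
- **Within cohort 1.** "In cohort 1, we shall also conduct a cost-utility analysis using quality-adjusted life years derived from the EQ-5D-5L".

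The Secondary Outcome Measures section places the utility instrument in one cohort: "patients in cohort 1 will also be assessed using the quality-of-life self-completion questionnaire EQ-5D-5L to determine overall improvement over time". The same section introduces the shared measures with "We shall also collect pragmatic efficacy, tolerability, and functional outcome measures in both cohorts". Its list covers admissions, emergency and outpatient contacts, drug and dose changes, side effects with BMI, and work or study. It contains no utility measure.

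The Participants section describes the comparison group: "Cohort 2 will be a retrospective, consecutive (in reverse chronological order as registered in the CAUSA electronic health records) sample of patients".

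Objective 4, under Objectives, asks whether the new model can bring cost benefits to public health care and the wider economy.

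**The concern.** A cost-utility analysis sets the extra cost of one option against the extra QALYs it yields over another. Here it is limited to the cohort that receives the new model, so nothing shows what QALYs the same kind of patient would have had without it.

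Patients enter follow-up when their initial maintenance antipsychotic is prescribed for a first episode of psychosis. Some improvement over the following year might occur under usual care too. A cost per QALY computed from cohort 1 alone cannot separate that improvement from the effect of PRINT. Objective 5 is a blueprint for wider adoption, so a cost-per-QALY figure without a counterfactual could be read as evidence of value when it is not.

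The name of the between-cohort analysis is a smaller matter. Cost-benefit analysis expresses outcomes in money, and the outcome named is discontinuation of the first antipsychotic.

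**Working it through.** The Economic Evaluation section states no numerical result or target, so there is no figure to reproduce. The check is which terms of the estimand the plan can supply.

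**Step 1. Incremental cost per QALY.**

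ICER = (C1 − C2) / (QALY1 − QALY2), with 1 for PRINT and 2 for usual care.

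| Term | Source in the protocol article | Available? |
|---|---|---|
| C1, C2 (12-month cost) | Service use schedule, both cohorts (Economic Evaluation) | Yes |
| QALY1 | EQ-5D-5L in cohort 1 (Secondary Outcome Measures) | Yes |
| QALY2 | Not in the shared measures; cohort 2 is retrospective; no external utilities or model named | No |

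The denominator cannot be formed.

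**Step 2. What cohort 1 alone can give.** The documents contain no utilities, so the values here are assumptions for illustration.

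- *Average ratio, C1 / QALY1.* If utility rises linearly from 0.5 to 0.8 over one year, QALY1 = (0.5 + 0.8) / 2 = 0.65. Of this, 0.50 is what a patient staying at the baseline level would have had anyway. The ratio is not incremental.
- *Before-after gain.* For a linear rise r over one year, the area above baseline is r / 2.
  - r = 0.3: 0.3 / 2 = 0.15 QALY
  - r = 0.1: 0.1 / 2 = 0.05 QALY
  - r = 0.4: 0.4 / 2 = 0.20 QALY

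If utility under usual care would rise linearly by r0 from the same baseline, the true increment is (r − r0) / 2, and the amount wrongly credited to PRINT is r0 / 2. With r = 0.3:

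| r0 | Before-after gain | True increment | Wrongly credited |
|---|---|---|---|
| 0 | 0.15 | 0.15 | 0 |
| 0.1 | 0.15 | 0.10 | 0.05 |
| 0.3 | 0.15 | 0 | 0.15 |

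The plan collects nothing that would say which row applies.

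**Step 3. What the two cohorts together can give.** Let D be the proportion who discontinue within one year. Then (C1 − C2) / (D2 − D1) is the incremental cost per discontinuation avoided. All four terms are planned in both cohorts, so it can be formed. It is a cost-effectiveness ratio. A net benefit in money would also need a money value per discontinuation avoided, and the article gives none.

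**The case against.** The strongest reply is that the cost-utility sentence is an add-on, openly limited to cohort 1. The article never promises an incremental cost per QALY or a QALY comparison between cohorts, and a journal article leaves much economic detail to the full protocol or analysis plan.

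Part of this stands. How costs and discontinuation are combined, and whether a money value is attached to a discontinuation, may well be set out elsewhere. The cost-benefit label is therefore only a note on naming. External utilities are not excluded either; the article simply names none. The missing comparator is different: the article expressly confines the analysis to one cohort and the instrument to that same cohort. That is a stated scope, and an analysis plan could supply a comparator only by adding to it.

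A reader might infer more than the document supports:

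- *That costs and outcomes are tabulated by cohort and never combined.* The text says they will be compared, and the method of combining them may be in the fuller document.
- *That the between-cohort analysis gives no answer on cost benefits.* Service use and work or study outcomes are planned in both cohorts, so the cost difference bears directly on objective 4 without any QALY.
- *That the cohort 1 cost per QALY will probably look favourable.* No cost, utility or threshold is given, so this cannot be known.
- *That a before-after cost per QALY is what is planned.* Describing the EQ-5D-5L as a measure of improvement over time makes this a possible reading, but the Economic Evaluation section does not specify it.

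It is also fair to say that cost per discontinuation avoided has limits. It gives no value-for-money verdict without a willingness to pay. The Limitations section itself warns that guided prescriptions may be kept despite poor efficacy or adverse events, so an avoided discontinuation is not necessarily a health gain.

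**Conclusion.** The point holds in a limited form. As written, the cohort 1 cost-utility analysis has no comparator QALYs and cannot yield an incremental cost per QALY. This follows from the stated scope and needs no assumption about data.

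The possible bias in a before-after version cannot be sized from the document. It equals half the usual-care rise in utility if paths are linear over one year from a common baseline, which is 0.05 to 0.20 QALY per patient for assumed rises of 0.1 to 0.4. That range illustrates one possible analysis and does not measure an error in the plan.

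The effect is confined to a secondary analysis. Objective 4 is partly affected, since the between-cohort comparison remains feasible. The primary outcome and its test are not affected.

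**What to change.** 1. Report cohort 1 mean 12-month cost and mean EQ-5D-5L scores and QALYs descriptively, with confidence intervals. State that no cost-per-QALY or value-for-money claim will be drawn from them. Alternatively, name an external comparator for usual-care utilities, state its assumptions and give a sensitivity range.
2. Base the economic conclusion on the comparison already planned between cohorts: the difference in mean 12-month cost and the difference in 1-year discontinuation, each with an interval, and the incremental cost per discontinuation avoided. Show the two differences beside the ratio, which becomes unstable when the difference in discontinuation is small. Read the result alongside the other pragmatic outcomes, given the status quo bias that the Limitations section acknowledges.
3. Call that comparison cost-effectiveness, or state the money value of a discontinuation that would make it cost-benefit.

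The cost is a change of wording and some routine interval estimation. The descriptive option needs no new data; the alternative needs outside utility values. The trial gives up a headline cost per QALY that it could not have supported. The Results section expects data collection to end by June 2027, with about six months of analysis, so the change can be made before the economic analysis is run.
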